### Intervention procedures

Twenty intervention sessions will be held over 4 consecutive weeks, with five sessions per week (Monday to Friday). A repetitive magnetic stimulator (Neurosoft LLC, [name]) and a figure-of-eight coil with a 70 mm diameter will be employed to administer iTBS over the left DLPFC (F3), following the 10–20 international EEG system (48). The subjects are required to wear a tight-fitting EEG cap, and the position of “F3” is marked using a mark pen. Three different sizes of EEG caps will be prepared for the purpose of target locating assistance, which will correspond to the following head circumferences: 46-50 cm (extra small), 50-54 cm (small), and 54-58 cm (medium). The magnetic coil was positioned at this point with an angle of approximately 45° to the interhemispheric line (49). A “sham coil” is employed to simulate the visual, auditory, and tactile aspects of rTMS without actually delivering any electromagnetic stimulation. The resting motor threshold of each participant was determined by stimulating the primary motor cortex until a 50 μV deflection of electromyogram or a visible twitch in the first dorsal interosseous muscle was identified in at least two of three trials (26, 50). One iTBS session consists of triplet 50 Hz pulses repeated in 5 Hz bursts for a total of 1800 pulses at 90% of the motor threshold (51). Sixty trains were applied in 2-second bursts with 8-second pauses. Previous research has found that three continuous sessions of iTBS with no interval (1800 pulses) over the primary motor cortex can reverse the effect from excitatory to inhibitory (52). Contrary to this motor cortex study, applying iTBS with 1800 pulses over the left DLPFC may act on DLPFC activity via the modulation of excitation/inhibition balance, which is similar to one regular session of iTBS (600 pulses) (53). The treatment will be administered in three sessions per day, with a 10-minute interval between each session (5400 pulses per day). The magnetic coil will be held by the experimenter as this is more comfortable for the subjects. During the rTMS administration, the subjects will be instructed to sit in a chair and refrain from moving. Children who are emotionally unstable or unable to remain seated are allowed to eat snacks, play with their favorite toys, or listen to music, while parents are encouraged to offer comfort and reassurance. Earplugs are provided for noise reduction. Younger children can be held by their parents or placed in a stroller for treatment. If adaptation remains challenging, parents are advised to bring their child to the treatment room daily over the next few days to acclimate them to the room environment and the noise and stimulation of TMS. For children who continue to be unable to tolerate treatment, they will be withdrawn from the trial. Once the child has acclimated to TMS treatment, eating snacks, playing with toys, or listening to music during the sessions will no longer be allowed. The children are allowed to rest between the three treatment sessions, during which they are free to play and interact with the parents and researchers. Furthermore, it is our intention to cultivate a positive relationship with the children.

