
### Assignment of interventions

This is a double-blind randomized clinical trial. The randomization of participants will be conducted using a computer-generated random list, based on the permutation block method with a random number generator. The ratio of participants allocated to each group will be 1:1. The allocation sequence was concealed by a research assistant using sealed, opaque envelopes that contained the treatment information prior to the study’s official commencement. Once the consent form and baseline measures have been completed, an envelope for a participant ID number will be provided to the rTMS therapist prior to the first iTBS session. The rTMS therapist is the sole individual responsible for determining the treatment method (iTBS or sham-iTBS), and he/she does not perform assessments or statistical analyses. It is imperative that other study researchers, participants, parents/guardians, and statistical analysts, remain completely blinded to the treatment condition. Any adverse or discomfort event will be recorded after each iTBS treatment session. If a participant experiences a serious adverse event, the blindness will be removed.

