### Sample size and recruitment

Forty children diagnosed with ASD will be included in total (iTBS group, n = 20; sham group, n = 20). Whilst a formal sample size calculation is not required in a pilot study (54), it is recommended that a sample size of between 15 and 20 participants is maintained for the purpose of conducting a subsequent full-scale study (55). In consideration of a potential dropout rate of 15%, the objective was to recruit a total of 48 participants. Nonetheless, we will endeavor to recruit a greater number of participants if feasible within the time and resources available. All participants will be recruited from the China Autism Rehabilitation Research Center, Beijing Boai Hospital, where advertisements will be posted to attract potential participants. One researcher will conduct the recruitment process, during which he/she will document the participants’ medical histories, including past and current medical conditions.

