### Outcome measures

For the first study objective, to determine feasibility and safety, we will report the recruitment rate, adherence rate, completion rate, and adverse reactions. The recruitment rate will be reported as the percentage of eligible ASD children who will participate in the study and the number of subjects recruited monthly over the recruitment period. The adherence rate will be measured by the proportion of participants who complete the intervention as planned. The completion rate will be assessed by the proportion of participants who complete all assessments and follow-ups. Safety will be assessed by comparing the rates of drop-outs attributed to adverse events and the rates of serious adverse events. For the second study objective, to determine the potential efficacy of the iTBS intervention on ASD, our endpoints include the Autism Behavior Checklist (ABC), Social Responsiveness Scale, 2nd Edition (SRS-2), Childhood Autism Rating Scale (CARS), Autism Treatment Evaluation Checklist (ATEC) and the Repetitive Behavior Scale-Revised (RBS-R). The ABC scale consists of 57 items that involve a range of typical autistic behaviors. These items are categorized into five domains including relating, sensory, language, body use and object manipulation, and social and self-help. Each item contained its own score ranging from 1 to 4 points according to the item weights, and higher total scores indicate more severe ASD symptoms (56) The SRS-2 is a norm-referenced quantitative assessment comprising 65 items pertaining to children’s behavioral characteristics. Parents or caregivers are required to rate five subdomains, namely social awareness, social cognition, social communication, social motivation, and restricted repetitive behaviors (57). The CARS was developed as an observational rating scale to capture ASD symptoms through parent/carer interviews, observations, and case reviews. Each item is scored from 1 to 4, with 1 representing appropriate behavior and 4 representing behavior that deviates severely from normal criteria, so higher total scores indicate more severe ASD symptoms. This tool can be utilized to display the overall symptom severity of ASD (58). The participant’s parent needs to complete the ATEC questionnaire, which is comprised of four subscales (speech/language communication, sociability, sensory/cognitive awareness, and physical/health/behavior). The ATEC has been used to measure treatment effects, with a lower score indicating a lower severity of ASD symptoms (59). The RBS-R was a valid tool for assessing repetitive and stereotypic behaviors in children with ASD, including six parts: stereotyped behaviors (6 items), self-injurious behaviors (8 items), obsessive-compulsive behaviors (8 items), ritualistic behaviors (6 items), fixation behaviors (11 items), and restrictive behaviors (4 items). The scale uses a 0-3 scoring system: 0 for no behavioral problems, 3 for severe, 2 for moderate, and 1 for mild (60).

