### Data analysis plan

All statistical analyses will be performed using IBM SPSS 26.0 by independent blinded statisticians. Chi-squared tests and t-tests will be performed for the categorical and continuous variables, respectively, to examine the group differences in the demographics and clinical profiles between the two groups at baseline. To assess for significant differences in treatment effects over time, a mixed-effects model with predictor variables for group (rTMS condition: active vs placebo) and time (baseline vs. end of treatment vs. follow-up) will be fitted to the data from the outcome measures. The effect size between groups will also be calculated. The feasibility and safety outcomes will be presented as proportions, and we will compare the rates between the two groups. All significance levels will be set at P < 0.05.

The EEG signals are preprocessed using the EEGLAB toolbox under MATLAB R2022b. A finite impulse response filter is constructed with a lower edge frequency of 1 Hz and a higher boundary frequency of 45 Hz. In order to artifacts induced by excessive body movements, we will perform an initial visual inspection of the EEG data. An independent component analysis will be conducted to remove additional artifacts. The segmentation will divide the EEG signals into epochs of 2s. The absolute and total power of the four frequency bands (δ, θ, α, and β) are calculated separately using the fast Fourier transforms. Then, the relative power of channels in these frequency bands will be calculated using MATLAB R2022b to analyze the changes in brain functional network characteristics before and after the intervention, including the magnitude squared coherence, phase locking value, phase lag index, and weighted phase lag index.

The NirSpark software package (Danyang HuiChuang Medical Equipment Co., Ltd., Zhenjiang, China) was used to analyze the fNIRS data. Following the conversion of the raw data to optical density signals, the motion artifacts will be reduced through the utilization of cubic spline interpolation. The obtained signals are filtered with a band-pass (0.01 to 0.2 Hz) filter in accordance with Butter’s law, to eliminate physiological noise generated by heartbeat and respiration. After preprocessing, the optical density will be converted to concentrations of oxyhemoglobin, deoxyhemoglobin, and total hemoglobin based on the Beer-Lambert law.

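### The only stated basis for judging safety is a comparison of two probably rare event rates between arms, under a general P < 0.05; 20 to 24 children per arm make that uninformative, so estimation with confidence bounds should replace it

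*Protocol article*

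**What the plan says.** - **Criterion.** Protocol article, Outcome measures: "Safety will be assessed by comparing the rates of drop-outs attributed to adverse events and the rates of serious adverse events". The Methods paragraph of the abstract repeats this. The same section also plans to report adverse reactions, but as a listed item rather than as part of the sentence that defines how safety is assessed.
- **Analysis.** Data analysis plan: "The feasibility and safety outcomes will be presented as proportions, and we will compare the rates between the two groups". That paragraph closes by setting every significance level at P < 0.05. It names no test for the safety rates; chi-squared is named only for baseline comparisons.
- **Size.** Sample size and recruitment sets 20 children per arm without a formal calculation, then adds: "In consideration of a potential dropout rate of 15%, the objective was to recruit a total of 48 participants". Assignment of interventions: "The ratio of participants allocated to each group will be 1:1".
- **Other safety data.** Assignment of interventions: "Any adverse or discomfort event will be recorded after each iTBS treatment session". Intervention procedures provides a withdrawal route for intolerance: "For children who continue to be unable to tolerate treatment, they will be withdrawn from the trial". Eligibility criteria has a further route for children who cannot cooperate.
- **Hypothesis and caveat.** The Introduction ends by hypothesising that high-dose iTBS may be feasible and safe. The Discussion concedes, in general terms, that the sample may be too small to show group differences.

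**The concern.** A between-arm test of two rare outcomes in a pilot of this size will usually be non-significant whether or not the intervention causes harm. Such a result does not separate a safe intervention from one with a material excess of events. No margin, acceptable rate or confidence bound is fixed, so the report would have only the comparison to set against the safety hypothesis.

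The children are 2 to 10 years old, the Introduction itself says that safety data for high-dose rTMS in children are scarce, and the results are meant to inform larger trials. An uninformative comparison could be carried forward as reassurance. The two chosen endpoints also leave out the events the Introduction leads one to expect: it cites an overall adverse-event prevalence of 25%, all mild and transient, and such events would seldom become serious events or drop-outs.

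**Working it through.** **Inputs from the protocol article.** 20 per arm for analysis; 15% dropout; 48 recruited; 1:1 allocation; significance level 0.05.

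**Assumptions.** Two-sided tests (sidedness is not stated). Fisher's exact test and the uncorrected chi-square are both shown, because no test is named for safety. The protocol gives no rate for serious adverse events or for drop-outs due to adverse events, so all true rates below are assumed.

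**1. The plan's own figure.** 40 / (1 − 0.15) = 47.06, rounded up to an even 48, or 24 per arm. The recruitment target reproduces. Drop-outs occur among those randomised, so 24 per arm is the natural denominator if the target is met. Both 20 and 24 are shown.

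**2. P values for k events against none.** With equal arms of n, Fisher's two-sided P = 2 × C(n, k) / C(2n, k). For 3 vs 0 at n = 20: 2 × 1140 / 9880 = 0.231. The uncorrected chi-square for 3 vs 0 is 40 × (3 × 20)² / (20 × 20 × 3 × 37) = 3.24, P = 0.072.

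| Events, active vs sham | Fisher, n = 20 | Chi-square, n = 20 | Fisher, n = 24 | Chi-square, n = 24 |
|---|---|---|---|---|
| 3 vs 0 | 0.231 | 0.072 | 0.234 | 0.074 |
| 4 vs 0 | 0.106 | 0.035 | 0.109 | 0.037 |
| 5 vs 0 | 0.047 | 0.017 | 0.0496 | 0.018 |

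Against no sham events, Fisher needs 5 active events and chi-square needs 4, at either size. Against one sham event they need 7 and 6.

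**3. Power.** With a true sham rate of 0%, power is the probability that a binomial(n, p) count in the active arm reaches 5 (Fisher) or 4 (chi-square).

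| Assumed true rates, active vs sham | n = 20, Fisher / chi-square | n = 24, Fisher / chi-square |
|---|---|---|
| 5% vs 0% | 0.3% / 1.6% | 0.6% / 3.0% |
| 15% vs 0% | 17% / 35% | 29% / 50% |
| 20% vs 0% | 37% / 59% | 54% / 74% |

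If some sham children also have events, power falls: for 20% vs 5% at 20 per arm it is 17% / 29%.

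**4. What no events would show.** The exact two-sided 95% upper limit for 0/n is 1 − 0.025^(1/n):
- n = 20: 16.8%
- n = 24: 14.2%

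**5. What estimation would show instead.** For 3/20 vs 0/20, the exact 95% interval for the active rate is 3.2% to 37.9%. The risk difference is 15 percentage points, with a 95% interval (Newcombe) of −3.8 to 36.0 points. The same data that give a non-significant P value show plainly that a large excess is not excluded.

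**The case against.** The strongest reply is that the protocol never links a non-significant P value to a finding of safety. It speaks of presenting proportions and comparing rates, the P < 0.05 line covers all analyses, the hypothesis says only that iTBS may be safe, and the Discussion warns about sample size. This stands. A reader might infer that the trial will declare iTBS safe on a non-significant test, but the text does not say so. The defect is that no other criterion is given, and the general caveat does not supply one.

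Second, a reader might infer that any large excess of harm would be missed. That is too strong. Uncorrected chi-square would flag 4 vs 0, Fisher would flag 5 vs 0, and recruiting 48 raises power. The 3 vs 0 result is non-significant by both tests at both sizes.

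Third, reporting of adverse reactions is already planned, events are recorded throughout, and the ethics committee oversees the study. This reduces the consequence but leaves the criterion as it is.

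Fourth, a reader might infer that intolerance withdrawals escape the safety count. Nothing says that such a withdrawal, if caused by a recorded adverse event, would not be attributed to it, and these children would lower the adherence rate. Merging non-cooperation with adverse-event drop-outs would mix behavioural refusal with harm, so it is not advised.

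Last, the choice of test and of intervals can be left to an analysis plan that is not shown. That is fair for detail, but the criterion itself and the significance level are fixed here.

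**Conclusion.** The point holds as a weakness in how safety is to be assessed; it does not show that the protocol will misread its result. With 20 or 24 children per arm, 3 events against none cannot reach two-sided P < 0.05 by Fisher or uncorrected chi-square. For a serious-event rate of 5% against 0%, power is at most 3%. The P values and the zero-event limits depend only on the arm sizes, two-sided testing and 95% confidence. The power figures rest on assumed true rates and depend on the test. Pilot status justifies the small sample, but it argues for estimation rather than a significance comparison.

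**What to change.** In Outcome measures and the Data analysis plan, and in the matching sentence of the abstract, replace the significance comparison for safety with estimation among all randomised and treated children:

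- For each arm, report any adverse event, drop-outs attributed to adverse events, and serious adverse events, each with an exact 95% confidence interval.
- Give risk differences between arms with 95% confidence intervals.
- List withdrawals for intolerance and for non-cooperation separately by arm, without adding them to adverse-event drop-outs.
- State that a non-significant difference is not evidence of safety, and word the safety conclusion on the upper confidence bound. For example, no serious adverse event in 24 active children would exclude only rates above 14.2%.

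The cost is analysis wording: adverse events are already recorded after each session, and no extra children or visits are needed. The downside is a less favourable safety statement.

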**Figure 3 f3:**
[figure not shown]
The channel layout and area of interest in functional near-infrared spectroscopy.

### Data collection and management

Upon enrolment, the names of participants will be replaced with a four-letter code in order to safeguard their privacy. The data will be recorded in the case report form, which encompasses the following information: demographics, patient history, baseline, post-treatment evaluation, and record of adverse events. Following the completion of each phase of data collection, the quantitative data will be entered into a Microsoft Excel spreadsheet. The data collection process will be conducted by an independent assessor who will be unaware of the participant allocation. The entered information will be protected by a password that will only be accessible to members of the research team. Any personal information provided by trial participants will be treated in strict confidence. All data will be stored securely for at least five years after completing the study.

### Data analysis plan

All statistical analyses will be performed using IBM SPSS 26.0 by independent blinded statisticians. Chi-squared tests and t-tests will be performed for the categorical and continuous variables, respectively, to examine the group differences in the demographics and clinical profiles between the two groups at baseline. To assess for significant differences in treatment effects over time, a mixed-effects model with predictor variables for group (rTMS condition: active vs placebo) and time (baseline vs. end of treatment vs. follow-up) will be fitted to the data from the outcome measures. The effect size between groups will also be calculated. The feasibility and safety outcomes will be presented as proportions, and we will compare the rates between the two groups. All significance levels will be set at P < 0.05.

The EEG signals are preprocessed using the EEGLAB toolbox under MATLAB R2022b. A finite impulse response filter is constructed with a lower edge frequency of 1 Hz and a higher boundary frequency of 45 Hz. In order to artifacts induced by excessive body movements, we will perform an initial visual inspection of the EEG data. An independent component analysis will be conducted to remove additional artifacts. The segmentation will divide the EEG signals into epochs of 2s. The absolute and total power of the four frequency bands (δ, θ, α, and β) are calculated separately using the fast Fourier transforms. Then, the relative power of channels in these frequency bands will be calculated using MATLAB R2022b to analyze the changes in brain functional network characteristics before and after the intervention, including the magnitude squared coherence, phase locking value, phase lag index, and weighted phase lag index.

The NirSpark software package (Danyang HuiChuang Medical Equipment Co., Ltd., Zhenjiang, China) was used to analyze the fNIRS data. Following the conversion of the raw data to optical density signals, the motion artifacts will be reduced through the utilization of cubic spline interpolation. The obtained signals are filtered with a band-pass (0.01 to 0.2 Hz) filter in accordance with Butter’s law, to eliminate physiological noise generated by heartbeat and respiration. After preprocessing, the optical density will be converted to concentrations of oxyhemoglobin, deoxyhemoglobin, and total hemoglobin based on the Beer-Lambert law.

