**Methods:**

A randomized controlled pilot trial with a 4-week intervention will be conducted. Forty children with ASD will be randomized into either the intervention or control group. The intervention group will receive 5400-pulse iTBS per day, while the control group will receive sham iTBS. Feasibility will be evaluated through recruitment, intervention adherence, and assessment completion. Safety will be assessed by comparing the rates of drop-outs attributed to adverse events and the rates of serious adverse events The efficacy outcomes include the Autism Behavior Checklist, Social Responsiveness Scale, 2nd Edition, Childhood Autism Rating Scale, Autism Treatment Evaluation Checklist and Repetitive Behavior Scale-Revised. Resting-state electroencephalogram and functional near-infrared spectroscopy will be employed to quantify alterations in functional brain connectivity and cerebral haemodynamics. Salivary levels of oxytocin, growth hormone, insulin-like growth factor 1, and insulin-like growth factor binding protein 3 are measured to reflect the biochemical response to iTBS. These indicators will be assessed at baseline and at the end of the intervention.

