In light of these evidences, we designed a pilot randomized controlled clinical trial to investigate the feasibility, safety, and efficacy of high-dose iTBS in children with ASD. We hypothesize that high-dose iTBS may be a feasible and safe rTMS protocol for children with ASD. A 4-week high-dose iTBS intervention, compared to sham stimulation, is expected to result in significant improvements in core autistic symptoms, alterations in resting-state functional connectivity, and changes in salivary levels of oxytocin, growth hormone, IGF-1, and IGFBP-3.

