## Discussion

To our knowledge, this study is the first to investigate the feasibility, safety, and efficacy of high-dose iTBS in children with ASD. We will assess recruitment, treatment adherence, tolerability, and safety of this modified rTMS protocol in the field of ASD. We will also examine its preliminary efficacy and provide novel information on brain function changes that occur during iTBS treatment. The insights gained from salivary oxytocin and growth-related factor assessments will contribute to a more profound comprehension of the role of iTBS in influencing the hypothalamic-pituitary system of ASD. If successful, larger-scale studies will be needed to ascertain the intervention’s efficacy with greater precision.

Several limitations should be noted. The study is currently being conducted on a feasibility scale and includes a small size which may be insufficient to detect significant differences between two groups. Relying solely on recruiting patients from the hospital may limit the generalizability of our findings. We decided to include children with ASD regardless of gender, subtype, and severity, leading to a heterogeneous population that may influence the study results. Last but not least, the lack of neuroimaging-guided target localization is a limitation of our iTBS program.

In conclusion, this trial will evaluate the feasibility, safety, and efficacy of high-dose iTBS treatment in children with ASD. The proposed study will provide pilot data to inform the feasibility and design of larger sample-size trials.

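### The efficacy model names group and time, with baseline as a level of time, but neither the group-by-time term that its aim needs nor a baseline adjustment

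*Protocol article*

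**What the plan says.** The Data analysis plan gives one sentence to efficacy inference. Its aim is "To assess for significant differences in treatment effects over time", and its means is "a mixed-effects model with predictor variables for group (rTMS condition: active vs placebo) and time (baseline vs. end of treatment vs. follow-up"). The section adds that a between-group effect size will be calculated, without saying from which term or visit. It names no interaction and no covariate.

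Two other statements matter:

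- **Baseline precedes treatment.** The Assignment of interventions section says "Once the consent form and baseline measures have been completed, an envelope for a participant ID number will be provided to the rTMS therapist", before the first stimulation session, and "The ratio of participants allocated to each group will be 1:1".
- **The number of visits differs between sections.** The Abstract, after listing the scales, EEG, fNIRS and salivary measures, says "These indicators will be assessed at baseline and at the end of the intervention". The model uses three levels, "time (baseline vs. end of treatment vs. follow-up"). The case report form in Data collection and management lists baseline and post-treatment evaluations, while the completion rate in Outcome measures also counts follow-ups. The schedule figure is not available here, so it may resolve this.

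**The concern.** A model that contains only a group term and a time term forces the arm difference to be the same at every visit, including the one before treatment. That cannot show whether the arms diverge over time, which is the question the sentence sets itself. Read literally, the group coefficient mixes the treatment effect with a baseline difference that randomisation makes zero in expectation.

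Several tests also stay open: the group main effect, the interaction, the contrast at end of treatment and the contrast at follow-up. The effect size is tied to none of them.

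The Introduction says the intervention "is expected to result in significant improvements in core autistic symptoms, alterations in resting-state functional connectivity, and changes in salivary levels" of the four hormones and growth factors, and the Discussion says the pilot data will inform larger trials. If a diluted coefficient were carried into that planning, the required sample would scale with the inverse square of the effect. A share of one-half would imply 1/0.5² = 4 times the sample, and a share of two-thirds 1/(2/3)² = 2.25 times.

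**Working it through.** **The plan's own figure.** The only design figure that can be recomputed is recruitment: 20/0.85 = 23.5, so 24 per arm and 48 in total, as stated. The article gives no effect size, SD, correlation or power, so all of these are assumptions below.

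**Inputs.** 20 per arm (Sample size and recruitment); 1:1 allocation; expected arm difference at baseline of 0; two visits (Abstract) or three (Data analysis plan); significance level 0.05, taken as two-sided.

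**Step 1: what the group coefficient estimates with main effects only.** With S the covariance matrix of the visits and d the vector of true arm differences, the coefficient has expectation w′d, where w = S⁻¹1 / (1′S⁻¹1). Under compound symmetry with equal variances, every visit has weight 1/k. As a share of the end-of-treatment effect:

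| Visits and pattern | Formula | Share | Simulated |
|---|---|---|---|
| 2 visits | (0 + 1)/2 | 0.50 | 0.49 |
| 3 visits, effect sustained | (0 + 1 + 1)/3 | 0.67 | 0.70 |
| 3 visits, half left at follow-up | (0 + 1 + 0.5)/3 | 0.50 | 0.48 |
| 3 visits, none left at follow-up | (0 + 1 + 0)/3 | 0.33 | 0.35 |

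The simulation used random-intercept fits with correlation 0.6 and 200 runs per row (Monte Carlo error about 0.02). Adding the group-by-time term and reading the baseline-to-end contrast gave 0.98 to 1.05 for a true value of 1.

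**Step 2: sensitivity to the covariance.** With first-order autoregressive correlation, three visits and a sustained effect, the share is 0.60 (r = 0.5) or 0.57 (r = 0.7). With two visits, an unstructured covariance and r = 0.5, it is 0.71 if the end-of-treatment SD is 0.8 of the baseline SD, and 0.29 if it is 1.25 times the baseline SD.

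**Step 3: precision if the interaction is intended.** In units of the outcome variance, per child:

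- change from baseline (unconstrained group-by-time contrast): 2(1 − r)
- baseline-adjusted comparison: 1 − r²
- ratio of adjusted to change: (1 − r²) / [2(1 − r)] = (1 + r)/2

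At r = 0.5 the ratio is 0.75, a 25% reduction. At r = 0.8 it is 0.90, a 10% reduction.

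**Step 4: illustrative power.** Assume an effect of 0.8 SD and use the normal approximation, power = Φ(effect/SE − 1.96) with SE = √(2v/20). The main-effect variance v is (1 + r)/2 with two visits and (1 + 2r)/3 with three. At r = 0.5 and two visits: v = 0.75, SE = √0.075 = 0.274, 0.40/0.274 = 1.46, and power is 0.31.

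| Test | r = 0.5 | r = 0.7 |
|---|---|---|
| Group main effect, 2 visits | 0.31 | 0.28 |
| Group main effect, 3 visits, sustained | 0.54 | 0.47 |
| Baseline-to-end interaction contrast | 0.72 | 0.90 |
| Baseline-adjusted arm difference | 0.83 | 0.94 |

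With an assumed effect of 0.5 SD and r = 0.5, the four rows become 0.15, 0.25, 0.35 and 0.45.

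**The case against.** The strongest reply is that the sentence names factors, not a complete model. It does not say main effects only, and it never calls the group coefficient the treatment effect. Its aim is the question that an interaction answers, so a reasonable analyst would include one. A journal article also condenses, and covariates and contrasts are often left to a fuller document that is not shown here.

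Much of this stands. A reader might infer that the trial will report about half of the true effect with power near 28%. The documents do not support that: it requires the literal additive reading, the two-visit schedule and equal variances. Under the three levels that the model itself lists, a sustained effect gives two-thirds. Nor do they show that a diluted effect size will reach the larger trial, because the effect size is not linked to any coefficient.

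A reader might also infer that the authors admit age as a source of heterogeneity and then ignore it. The Discussion does describe recruitment as "leading to a heterogeneous population that may influence the study results", but the features it names are gender, subtype and severity. The 2–10 year range appears in Eligibility criteria, where it is justified by feasibility and by avoiding pubertal effects.

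The reply does not remove the point. The article chose to list its predictors and time levels, and the listed terms do not serve the stated aim. Even on the charitable reading, a more precise estimate is available from data already being collected.

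**Conclusion.** The point holds as a specification that needs correcting, not as a demonstrated bias. On the literal reading, the group coefficient recovers about 0.50 of the end-of-treatment effect (two visits) or 0.67 (three visits, sustained effect), falling to 0.33 if nothing remains at follow-up. These shares assume equal variances and compound symmetry and move materially without them. On the intended-interaction reading there is no bias, and the loss is one of precision: a variance reduction of 25% to 10% is forgone for assumed correlations of 0.5 to 0.8.

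Severity is moderate. Feasibility and safety are the first objective, efficacy is the second, and the Discussion concedes that the sample may be too small to detect differences. Every power figure above rests on an assumed effect and correlation.

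**What to change.** Replace the model sentence with wording such as:

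> The treatment effect for each efficacy outcome is the active-minus-sham difference at end of treatment, estimated from a model adjusted for the baseline score (ANCOVA, or a mixed model with group-by-time and a common baseline mean), and reported with its 95% CI. The between-group effect size is computed from this contrast.

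Then state once whether a follow-up assessment exists and, if so, for which outcomes and when. Align the Abstract, Outcome measures, Data collection and management, and Data analysis plan with that statement. If follow-up is kept, report its contrast separately from the one at end of treatment.

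An age covariate is optional. If it is wanted, it should be prespecified on its own grounds and not on the heterogeneity limitation.

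The cost is a sentence or two of text and one degree of freedom for the baseline covariate. No new data are needed for the end-of-treatment contrast.
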